**Results::**

This study is ongoing and will be submitted to a peer-reviewed journal for publication once completed.

**Conclusion::**

A novel neutrophil-related inflammatory mechanism will potentially be identified. In addition, the study results will provide a safe, effective, simple and operational *Baduanjin* exercise protocol for moderate-to-severe COPD patients aimed at improving prognosis and quality of life.

## 1. Introduction

Globally, chronic obstructive pulmonary disease (COPD) is a disabling and progressive lung disease with recurrent symptomatic dyspnea, resulting in a high rate of re-hospitalization, mortality, and disability. It is anticipated that by 2030, COPD will be the third leading cause of death worldwide, resulting in a heavy social and economic burden.^[1–3]^ When treating COPD, it is important to focus on improvement of symptoms, reduction of the frequency and severity of exacerbations, and improvement in exercise tolerance and health status.^[4]^ However, there are no specific treatments for preventing and reversing the decline in lung function. Therefore, effective new approaches are urgently needed to improve the prognosis and quality of life of patients with COPD.

With the rapid development of the Internet and advanced technology, telemedicine and telecare models have been adopted globally as new medical services beneficial for earlier diagnosis, treatment, and improved self-management in chronic diseases.^[5]^ Telemedicine may be a suitable and crucial method for the delivery of remote education or other interventions in China because of its large population and shortage of medical resources.^[6]^ Compared with the usual home-based model, telemedicine and telecare models provide new alternatives to hospital-based care, with a virtual ward that can monitor respiratory function and improve the management of COPD, including early detection of acute exacerbations and improved health-related outcomes.^[7]^ Furthermore, post-discharge telemonitoring services could decrease COPD-related hospital re-admissions and mortality rates derived from acute exacerbation.^[8,9]^ Since December 2019, the global number of cases of coronavirus disease 2019 (COVID-19) has been rapidly increasing. Given the importance of avoiding person-to-person transmission during the COVID-19 pandemic, remote home monitoring combined with rehabilitation treatment may help keep patients with COPD or other chronic diseases safe, and this has been recognized by the Global Initiative for Chronic Obstructive Lung Disease (GOLD) guidelines.^[10]^

Pulmonary rehabilitation (PR) is an important non-pharmacological treatment that significantly improves symptoms, quality of life, and exercise capacity in patients with COPD. Of note, exercise training has been recognized as one of the core interventions.^[11]^
*Baduanjin* Qigong is a traditional Chinese exercise regimen involving relaxation and slow movements, without the limitations derived from equipment or venue availability. *Baduanjin* exercise or other subtypes of Qigong have both psychological and physical benefits in patients with various chronic illnesses, including cardiovascular disease,^[12]^ musculoskeletal pain,^[13]^ and cancer.^[14]^ Although many studies have reported on the application of *Baduanjin* in patients with COPD,^[15]^ its efficacy, safety, and mechanism of action as a complementary exercise therapy have not been evaluated to this date.

A recent meta-analysis concluded that *Baduanjin* exercise could improve exercise capacity, lung function, and quality of life in COPD patients,^[16,17]^ but the assessment criteria were not comprehensive, the potential mechanisms of action were not investigated, and there was no valid comparison of *Baduanjin* with traditional PR. Therefore, the aim of this study is to evaluate the efficacy and safety of *Baduanjin* in patients with moderate-to-severe COPD (BROCADE) in a multicenter randomized controlled trial (RCT) setting under home remote monitoring, and to explore the underlying neutrophil-related inflammatory mechanism. Novel mechanisms and evaluation methods will be determined.

## 2. Methods

### 2.1. Design and registration

This will be a pilot multicenter, open-label, prospective, randomized controlled clinical trial aiming to evaluate the efficacy and safety of *Baduanjin* in patients with moderate-to-severe COPD under remote monitoring and to explore the possible mechanisms involved in remission of the inflammation. After qualified recruitment, screening, and random assignment, a total of 150 participants from the Department of Respiratory Medicine of three teaching hospitals in Nanjing (China) will be included. All participants will be provided routine medication and lifestyle intervention, and they will be randomly assigned to one of three groups: a control group that will receive education on *Baduanjin* exercise, a classical PR group, and a *Baduanjin* group that will undergo a remotely monitored *Baduanjin* exercise program. The primary and secondary outcomes will be measured at baseline and at the cutoff point every 4 weeks. The exercise will be conducted at the outpatient clinic and monitored by a smartphone-based remote rehabilitation software program. The exercise program will last for 12 weeks, and the patients will be followed up for 24 weeks.

This work follows the Standard Protocol Items: Recommendations for Intervention Trials (SPIRIT).^[18]^ The flow chart of the participation screening process is shown in Figure 1, and the time points for enrollment, interventions, and assessments are shown in Figure 2. The study protocol has been registered with the Chinese Clinical Trial Registry (ChiCTR2100042700, http://www.chictr.org.cn/showproj.aspx?proj=120859).

**Figure 1. F1:**
[figure not shown]
Flowchart of the study design. COPD = chronic obstructive pulmonary disease, PR = pulmonary rehabilitation.

**Figure 2. F2:**
[figure not shown]
SPIRIT chart of the time points. 6MWD = 6-min walking distance, COPD = chronic obstructive pulmonary disease, CT = computed tomography, IL = interleukin, MPO = myeloperoxidase, NE = neutrophil elastase, PR = Pulmonary rehabilitation, TGF-β = transforming growth factor β, TNF-α = tumor necrosis factor α.

### 2.2. Sample size calculation

As documented previously, the primary outcome of the current study will be the 6-min walking distance (6MWD) at 12 weeks. According to a literature review, traditional Chinese exercise regimen was reported to be superior to the control intervention in the improvement of cardiopulmonary function when assessed using the 6MWD (580 ± 52.5 m in the *Tai Chi* group vs 564 ± 68 m in the control group, *P *= .035).^[19]^ In addition, significant improvement was observed in the PR group as compared to the control group (472 ± 62.56 m in the PR group vs. 355.49 ± 56.72 m in the control group, *P *< .001). We hypothesized that *Baduanjin* and PR would be superior to the control intervention in the improvement of cardiopulmonary function. Therefore, a sample of 40 to 43 patients (based on the estimation of data from Polkey et al^[19]^) could be assumed to have 80% power to detect significant differences between groups (*P* = .05, two-sided), with 20% inflation to account for dropouts. As a three-arm designed RCT, we adopted 50 patients per center (a final sample size of 150) to power the effect size of pre-specified interventions. The Power Analysis and Sample Size (PASS) software (v. 15.0.5; NCSS, LLC, Kaysville, UT) will be used in this study.

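### The stated 80% power does not follow from the printed inputs: 40 to 43 per group give about 21–23% power for the cited 16 m difference in 6MWD, which would need about 228 per group

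*Protocol article*

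**What the plan says.** Section 2.2 of the protocol article (Sample size calculation) states that "the primary outcome of the current study will be the 6-min walking distance (6MWD) at 12 weeks". It cites two sets of results:

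- Tai Chi against control: "580 ± 52.5 m in the *Tai Chi* group vs 564 ± 68 m in the control group", with a reported P of .035.
- Pulmonary rehabilitation (PR) against control: "472 ± 62.56 m in the PR group vs. 355.49 ± 56.72 m in the control group".

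It hypothesises that both Baduanjin and PR will beat control. Naming the Tai Chi study as the source of the estimate, it concludes that "a sample of 40 to 43 patients" "could be assumed to have 80% power to detect significant differences between groups", at a two-sided 5% level and with a 20% allowance for dropout. It then says "we adopted 50 patients per center (a final sample size of 150) to power the effect size of pre-specified interventions".

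Section 2.2 prints no other effect size, change-score SD or baseline correlation. Section 2.12 plans an analysis of variance across the three groups and reserves covariance analysis for data that are unequal at baseline.

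**The concern.** A difference of 16 m against SDs of 52.5 and 68 m is a small standardised effect, and around 40 patients per group cannot detect it with 80% power. The planning basis and the claimed power therefore appear incompatible by a wide margin.

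The stake is how the Baduanjin result will be read. If the true benefit equals the cited 16 m, the design would miss it nearly four times in five. Readers told that the trial had 80% power could take a non-significant result as evidence that Baduanjin does not help, although the trial could not reliably see the effect it was planned on.

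Two smaller points sit in the same paragraph. The size is set per center although the comparisons are between arms, and the dropout allowance reaches 50 only from the lower end of the 40 to 43 range.

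**Working it through.** **Inputs, all from section 2.2.** Means 580 and 564 m; SDs 52.5 and 68 m; two-sided alpha .05; power 80%; 40 to 43 patients; 20% dropout; 150 patients in three arms. The text does not say whether 40 to 43 is per group. I take it as per group, which fits 3 × 50 = 150 and favours the protocol.

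**Effect size.**
- Difference = 580 − 564 = 16 m
- Pooled SD = √[(52.5² + 68²)/2] = √[(2756.25 + 4624)/2] = 60.75 m
- d = 16/60.75 = 0.263

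**Attempt to reproduce 40 to 43 at 80% power.** The normal approximation is n per group = 2(1.960 + 0.842)²/d² = 2 × 7.85/0.0694, about 226.3, so 227. The exact two-sample t test gives 227.2, so 228. The stated figure is not reproduced; the shortfall is more than fivefold (228/43 = 5.3).

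**Power at the planned sizes.** Approximate power = Φ(d√(n/2) − 1.960):

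| Evaluable per group | d√(n/2) | Power, normal approx. | Power, t test |
|---|---|---|---|
| 40 | 1.178 | 21.7% | 21.4% |
| 43 | 1.221 | 23.0% | 22.7% |
| 50 | 1.317 | 26.0% | 25.6% |

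**Other readings tried for the 16 m difference (n per group for 80% power).**

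| Reading | n per group |
|---|---|
| SD 52.5 m in both groups | 170 (power 27% at 40) |
| SD 68 m in both groups | 284 (power 18% at 40) |
| One-sided .05 | 179 |
| One-sample or paired formula with the printed SDs | 85–142 |
| Three-group ANOVA, means spanning 16 m | at least 210 |

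If 40 to 43 were the total for two groups, power would be about 13%.

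**The PR contrast.** Difference = 472 − 355.49 = 116.51 m; pooled SD = √[(62.56² + 56.72²)/2] = 59.71 m; d = 1.95. About 6 per group suffice by the t test (5 by the normal approximation), so this contrast does not give 40 to 43 either.

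**What the planned size can detect.** With 40 per arm, the difference with 80% power is about (1.960 + 0.842) × 60.75 × √(2/40) = 38.1 m, or 38.5 m by the t test. That is 38.5/16 = 2.4 times the cited difference. By the t test it is 37.1 m with 43 per arm and 34.4 m with 50.

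**Dropout.** 40/(1 − 0.2) = 50, which matches. For 43 the answer is 43/0.8 = 53.75, so 54, or 43 × 1.2 = 51.6, so 52; 50 falls short of both.

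**The case against.** The strongest objection is that the sponsor may have used a quantity that the article does not print, such as the SD of within-patient change. There is a hint of this. The printed means and SDs give P = .035 only with about 128 per arm, whereas with 40 per arm they give P = .24, so the cited P value may come from a different analysis. An SD of about 25.5 m (40 per group) to 26.5 m (43 per group) would give 80% power for 16 m. This possibility means the claim should be tied to the printed inputs. It does not rescue the text: no such SD is given, and reaching it from 60.75 m by baseline adjustment requires a correlation of √[1 − (25.54/60.75)²] = 0.91 at 40 per group, or 0.90 at 43. Section 2.12 does not plan routine baseline adjustment.

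Second, the shortfall is not general. PR against control is amply powered, and an omnibus test with differences of 0, 16 and 116.51 m has power above 99% at 40 per arm. That stands, but the PR arm drives that power, which says nothing about Baduanjin against control.

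Third, section 2.1 calls the trial a pilot. That softens the consequence, but section 2.2 still makes an explicit power claim and section 3 anticipates efficacy conclusions.

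Fourth, the unit and dropout remarks are minor. That is fair: three centers and three arms both give 150, and 50 is exactly right for 40 evaluable.

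**Conclusion.** The concern holds. On the inputs that section 2.2 prints and names as its basis, 40 to 43 evaluable patients per group give about 21–23% power for Baduanjin against control, not 80%. About 228 evaluable per group would be needed.

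This rests on a two-sided 5% two-sample comparison of week-12 means, the pooled printed SD, equal allocation and no multiplicity adjustment. Using either printed SD alone moves power at 40 per group only between 18% and 27%. Splitting alpha over two comparisons (.025 each) would lower power further, to 14–15% at 40 to 43 per group. The conclusion would change only with an SD of about 25–26 m for the analysed quantity, which the document does not state.

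**What to change.** Keep 150 patients and restate section 2.2 as follows:

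- 50 patients randomised per arm, with about 40 evaluable after 20% dropout (50 × 0.8). Replace the per-center unit by the arm.
- For Baduanjin against control, 80% power at two-sided .05 for a difference of about 38.5 m, assuming an SD of 60.7 m. Present this as the detectable difference at the chosen size, not as an expected effect.
- Power for the cited 16 m difference is about 21%.
- A non-significant result does not exclude differences of the size cited.

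If the 40 to 43 came from a different SD or a change-score analysis, print that figure and its source, and make the analysis in section 2.12 match it.

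The cost is wording only; the stated power becomes less favourable. By contrast, truly powering for 16 m would take 228/0.8 = 285 randomised per arm, or 855 in all, which is not proposed here.

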### 2.3. Participant recruitment strategy

Individuals were recruited via poster or WeChat invitation in collaboration with three participating centers from January 2021 to June 2021. Additionally, potential participants were recruited using clinical databases at the three teaching hospitals by phone or face-to-face interviews. After being provided with information about the study, individuals who agree to participate will be asked to attend the screening evaluation.

### 2.4. Inclusion criteria

The inclusion criteria are a diagnosis of clinically stable COPD, and severity of airflow limitation classified as moderate-to-severe (30% ≤ forced expiratory volume in 1 s, [FEV_1_]_ _< 80% predicted value) based on post-bronchodilator FEV_1_, according to the GOLD criteria^[20]^; age of 40 to 75 years; ability to complete exercise training; ownership of a smartphone and ability to use it; no participation in other clinical trials in the past 6 months; no current participation in daily exercise, such as *Baduanjin*, *Tai Chi*, and aerobic exercises; and willingness to participate in research and sign the written informed consent form.

### 2.5. Exclusion criteria

The exclusion criteria are mild COPD (FEV_1 _≥ 80% predicted value) or very severe COPD (FEV_1 _< 30% predicted value); coexisting airway obstruction caused by asthma or other non-chronic obstructive pulmonary diseases; severe comorbidities, such as cardiovascular, kidney, or liver disease, malignant tumors, hematopoietic diseases, endocrine diseases, or mental illness; uncontrolled chronic diseases, including hypertension (resting blood pressure ≥ 160/100 mm Hg), diabetes (random blood glucose > 16.7 mmol/L, glycosylated hemoglobin > 7.0%); patients who are breastfeeding or pregnant or plan to become pregnant during the study period; lack of general athletic ability, including the upper and lower limbs; poor compliance, difficulty in cooperating with assessment, training, and treatment; and participation in any PR program within 4 weeks prior to enrollment or plan to participate in other PR programs during the study period.

### 2.6. Randomization

Statisticians who will not participate in the study will use the SPSS software (v. 24.0; IBM Corp., Chicago, IL) to generate random numbers, which will be placed in lightproof envelopes. Eligible participants will be assigned an envelope with group information.

### 2.7. Interventions

All participants will be given routine medication and lifestyle intervention, and they will be randomly assigned to one of three groups: a control group, which will receive health education involving exercise methods, health regimens, and nutrition The participants will receive a health education brochure and will be followed up by phone call to discuss physical activity, disease progression, health status, and psychological status; a classical PR group, which will undergo PR training in the outpatient clinic, including power bicycle training, upper limb resistance training, and lower limb resistance training; and a *Baduanjin* group, which will perform *Baduanjin* exercise, displayed by video instructions on the participants’ smartphones installed with a remote rehabilitation software (Sukang R + health App, v. 5.1.40.0, Chengdu Shangyi Information Technology Co., Ltd., Chengdu, China) whilst wearing a heart rate belt (RecoveryPlus H1, Chengdu Shangyi Information Technology Co., Ltd.), which will be monitored remotely. Before the start of the experiment, professionals from Nanjing University of Traditional Chinese Medicine will teach the *Baduanjin* exercise (version from the General Administration of Sports) until the participants master the correct posture and stretching. Eight forms of *Baduanjin* Qigong exercise are shown in Figure 3. In both the PR and *Baduanjin* groups, the exercise intervention regimen will need to be performed for a cumulative time of 1 h per day, three times per week for 12 weeks.

**Figure 3. F3:**
[figure not shown]
Eight forms of *Badunjin* Qigong exercise.

### 2.8. Efficacy assessments

The effects of *Baduanjin* exercise, including clinical symptoms, quality of life, activity and endurance, lung function, and respiratory muscle function, will be evaluated in patients with moderate-to-severe COPD and compared with the effects of the control and PR interventions. The primary outcomes will include the 6MWD and the St. George’s Respiratory Questionnaire index. The secondary outcomes will include lung function test results, including FEV_1_, forced volume capacity (FVC), ratio of FEV_1_ to FVC (FEV_1_/FVC%), maximum expiratory flow rate, and maximum ventilation per minute; chest high-resolution computed tomography to compare the cross-sectional area of the pectoralis major and subcutaneous fat; Modified Medical Research Council scale; COPD assessment test questionnaire results; lower extremity muscle strength; and Short-Form 36-item Health Survey for healthy living results.

### 2.9. Safety assessments

Although *Baduanjin* exercise is non-strenuous, easy to learn and practice, and unlikely to cause injury,^[21]^ we will evaluate its safety. During the process of exercise intervention, we will monitor the heart rate, finger pulse oxygen saturation, and adverse events (such as dyspnea, dizziness, falls, muscle strain, or COPD exacerbation) of each participant in real time. If any of the above events occur, the training will be stopped, and we will provide professional medical care, emergency observation, or hospitalization in severe cases. These events will be treated as reasons for automatic withdrawal from our study to comply with ethical rules. The details of adverse events will be recorded in the case report file and will be reported to the Ethics Committee within 24 hours.

### 2.10. Exploration of novel inflammatory mechanism

To characterize the inflammatory process in the participants, and the impact of the exercise program on it, 20 mL of elbow venous blood will be centrifuged and the serum will be used to detect common inflammatory cytokines by enzyme-linked immunosorbent assay, including interleukin (IL)-6, IL-8, IL-10, tumor necrosis factor-α, and transforming growth factor-β. Previous studies have confirmed that neutrophils play a pivotal role in the development and progression of COPD; however, the underlying mechanism remains unclear. Therefore, we will collect induced sputum from the participants to identify inflammatory cells by cell smear and staining techniques, including myeloperoxidase, neutrophil elastase, and histone citrullination of neutrophil extracellular traps (NETs) by enzyme-linked immunosorbent assay or western blotting. The expression of sialic acid-binding immunoglobulin-like lectin 9 (Siglec-9) will be tested by western blotting of samples obtained from the peripheral blood of the participants.

### 2.11. Data management

The statistician will randomize subjects into different groups and perform the statistical analyses. The Clinical Practice Center of three teaching hospitals will be responsible for monitoring research progress and securely storing the data and records. Only authorized research assistants will have access to the trial data.

### 2.12. Statistical analysis

Statistical software (SPSS version 24.0, SPSS, IL) will be used for statistical analysis in this study. All data will be presented as descriptive row statistical analyses (mean ± standard deviation). For comparisons between the three groups, analysis of variance will be used in cases in which the normal distribution and homogeneity of variance assumptions have been verified; otherwise, the Wilcoxon rank sum test will be used. For intra-group comparisons, an independent sample *t* test will be used in cases in which the normal distribution and homogeneity of variance assumptions have been verified; otherwise, a paired sign rank sum test will be used. For baseline unequal data, the two groups will be compared by covariance analysis. Additionally, statistical data will be used to calculate the composition ratio and the rate of each indicator. The total effective rate will be compared between the groups using the c*hi*-squared test. Statistical significance will be set at *P* < .05.

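### The named ANOVA for week-12 6MWD uses neither the week-4 and week-8 visits nor, by default, baseline: a certain loss of precision, and bias only if dropout is selective by arm

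*Protocol article*

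**What the plan says.** Four statements in the protocol article bear on this point.

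- **Endpoint (2.2):** "the primary outcome of the current study will be the 6-min walking distance (6MWD) at 12 weeks". Section 2.8 adds a second one: "The primary outcomes will include the 6MWD and the St. George’s Respiratory Questionnaire index". No time point is given there for the questionnaire.
- **Dropout (2.2):** the sample size is set "with 20% inflation to account for dropouts", and the final total is 150.
- **Visits (2.1):** "The primary and secondary outcomes will be measured at baseline and at the cutoff point every 4 weeks". I read this as baseline and weeks 4, 8 and 12 during treatment. The wording is loose, and the visit chart (Figure 2) is not available to check it.
- **Test (2.12):** "For comparisons between the three groups, analysis of variance will be used in cases in which the normal distribution and homogeneity of variance assumptions" are verified, and a rank test otherwise. Covariance analysis appears only for data unequal at baseline, and for two groups. No repeated-measures term is named.

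**The concern.** The design collects each patient's course, but the stated test looks at one value per patient. An ANOVA of week-12 6MWD ignores the visits before it. A patient who leaves after week 4 or week 8 contributes nothing unless a value is imputed. Baseline 6MWD, usually the strongest predictor of later 6MWD, enters only if the arms happen to differ on it.

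Two things are at stake. The first is precision, which this trial can ill afford: the treatment difference quoted in 2.2 for a traditional Chinese exercise is 16 m against an SD of about 60 m. The second is possible bias. The arms carry unequal burdens (2.7): three 1-hour sessions a week for 12 weeks in the exercise arms, against a brochure and phone calls in control. Section 2.9 also makes adverse events during exercise, including dyspnea and exacerbation, a reason for withdrawal from the study. Missingness could therefore differ between arms in ways related to walking distance.

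**Working it through.** **Inputs from the protocol (2.2).** Exercise 580 m, SD 52.5; control 564 m, SD 68. The difference is 580 − 564 = 16 m. The pooled SD is √[(52.5² + 68²)/2] = 60.7 m. Dropout 20%; total 150.

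**The plan's own figures.** The text gives "a sample of 40 to 43 patients (based on the estimation of data from" the cited study), without saying whether this is per arm or already inflated.
- The dropout step fits if 40 is the evaluable number per arm: 40/(1 − 0.20) = 50, and 3 × 50 = 150.
- The 40 to 43 itself does not follow from 16 m and 60.7 m. For 80% power at two-sided 0.05, 2 × (1.96 + 0.84)² × 60.7²/16² gives about 227 per arm. That is a separate matter and is not pursued here.

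**Patients without a week-12 value.** 0.20 × 50 = 10 per arm, leaving 40. The 50 per arm is inferred from 150/3, since 2.2 words it as 50 per center.

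**Standard error of the ANOVA contrast.** With 40 evaluable per arm: 60.7 × √(2/40) = 13.6 m. The simulations below gave 13.5 to 13.7 m.

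**Effect of baseline adjustment alone.** Assume correlation between adjacent visits of 0.70 to 0.85, decaying with distance (not in the documents). The baseline-to-week-12 correlation is then 0.70³ = 0.343 to 0.85³ = 0.614, and the standard error is multiplied by √(1 − r²):
- correlation 0.70: 13.6 × √(1 − 0.118) = 12.8 m
- correlation 0.85: 13.6 × √(1 − 0.377) = 10.7 m

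**Effect of the intermediate visits, and bias.** Two-arm trials (Baduanjin versus control) were simulated, 4,000 per scenario, under these conditions:
- 50 per arm, SD 60.7 m, and a linear build-up to a true 16 m;
- 20% dropout, all of it before week 8 or week 12;
- in the selective scenario, dropout in the exercise arm weighted to patients with small early change (assumed odds ratio about 1.6 to 2.7 per SD) and random in control.

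| Analysis | Mean estimate, selective dropout in exercise arm only | Standard error |
|---|---|---|
| Week-12 ANOVA, completers | 17.4 to 19.1 m | 13.5 to 13.7 m |
| Baseline-adjusted completers | 18.6 to 21.5 m | about 10.7 to 12.8 m (formula above) |
| Longitudinal likelihood model | 15.8 to 16.1 m | about 10 to 12.7 m |

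- The ANOVA shift is about +1.5 to +3 m, or 9% to 20% of 16 m. Against its own standard error it is 1.5/13.5 = 0.11 to 3/13.5 = 0.22.
- The shift for baseline-adjusted completers is larger, +2.5 to +5.5 m. Adding baseline alone therefore does not remove this bias.
- With random dropout, or dropout equally selective in both arms, every method returned about 16 m.
- By symmetry, if the same selection acted only in control, the ANOVA estimate would fall by the same 1.5 to 3 m, to about 13 to 14.5 m.
- The longitudinal model's gain in standard error over baseline-adjusted completers was only about 1% to 5%.

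**The case against.** The strongest reply is that 2.12 does not say complete-case. ANOVA can be run on imputed data, and analysis sets and missing-data rules may sit in a statistical analysis plan or full protocol that is not shown. This stands. The point must rest on the test that is named, not on a missing-data rule that is absent. The named test still takes no account of the intermediate visits, and uses baseline only on a condition.

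A reader might go further and infer that the Baduanjin effect will be overstated. The documents do not support that. Nothing in them says that poor responders will leave the exercise arms and not control. In an open-label trial, worsening or disappointed controls could leave too, which would push the estimate down. Against pulmonary rehabilitation, also an exercise arm, the direction is open.

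Three further objections hold in part.
- The simulated dropout depended on observed early change, which is the condition under which the longitudinal model is unbiased. Its return to 16 m is therefore expected, not evidence that it would cope with every cause of dropout. In particular, withdrawals under 2.9 after an acute event need not be predicted by earlier 6MWD.
- Every simulated patient had a week-4 value. Real patients may leave before then, and the model does not recover them.
- Most of the precision gain could be had from baseline adjustment alone. That is true, but 2.12 does not make such adjustment the default either.

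**Conclusion.** The point holds as a mismatch between a stated test and the stated design. The part that does not depend on the dropout mechanism is precision: a standard error of about 13.5 m against about 10 to 12.7 m. This rests on the protocol's SD, 50 per arm, 20% dropout and assumed adjacent-visit correlations of 0.70 to 0.85. Most of the gain comes from baseline and only a few percent from weeks 4 and 8.

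Bias is a possibility, not a finding. It arises only if dropout is related to early response differently between arms and values are not imputed. In the illustrated case for Baduanjin versus control it is about +1.5 to +3 m on 16 m, small beside the standard error. It vanishes under random or equally selective dropout, and it can reverse. The change is worth making because it replaces a stated method with a better one on data already planned. Confidence is moderate.

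**What to change.** In 2.12, make the primary analysis of 6MWD and of the St. George's questionnaire a mixed model for repeated measures:

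- fixed effects for arm, visit (weeks 4, 8, 12), arm-by-visit and the baseline value of the outcome;
- unstructured covariance across visits;
- all randomised patients with at least one post-baseline value;
- week-12 arm contrasts as the primary result. For the questionnaire, week 12 is taken over from 6MWD and should be stated.

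Keep the week-12 ANOVA as a sensitivity analysis, and add one that allows for missing-not-at-random dropout.

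The cost is wording. No visits or patients are added, provided 2.1 means what it appears to mean, and the SPSS software named in 2.12 can fit the model through its MIXED procedure. The downside is that the model assumes dropout is explained by observed values, which cannot be tested, and it does not recover patients lost before week 4. Both are reasons to keep the sensitivity analyses.

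### The main between-arm test named is an omnibus three-group ANOVA with no Baduanjin contrast, and its rank-based fallback is a two-sample test

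*Protocol article*

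**What the plan says.** Section 2.12 (Statistical analysis) gives the main comparison of the arms: "For comparisons between the three groups, analysis of variance will be used" when normality and equal variance have been verified; "otherwise, the Wilcoxon rank sum test will be used". It names no pair of arms, no follow-up procedure and no multiplicity rule; the significance level is .05 throughout.

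The same section names two further between-arm analyses. One is conditional on the baseline: "For baseline unequal data, the two groups will be compared by covariance analysis". The other is a chi-squared test: "The total effective rate will be compared between the groups using the" chi-squared statistic, for an outcome that is not among those listed in section 2.8.

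The questions are put elsewhere, in pairs. Section 2.2 hypothesizes that Baduanjin and PR "would be superior to the control intervention in the improvement of cardiopulmonary function". The Introduction gives as one reason for the trial that, in earlier work, "there was no valid comparison of *Baduanjin* with traditional PR". The Discussion says that Baduanjin will be set against both control and PR.

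**The concern.** An omnibus ANOVA tests the hypothesis that all three means are equal. Rejecting it says that at least one arm differs, not which one. One of the three arms here is an established active treatment for which the protocol itself quotes a very large effect, so rejection is to be expected whatever Baduanjin does. A significant overall result could then be read as support for Baduanjin while carrying no information about it.

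The fallback raises a second problem. The rank sum test takes two samples. As written it cannot be applied to three groups, so someone must decide at the analysis stage whether a three-group rank test or a set of pairwise tests was meant. These test different hypotheses and have different error rates, and the choice would arise only after the distributions had been inspected.

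**Working it through.** **1. Inputs.** All are from section 2.2 unless marked as assumptions.
- PR effect: 472 − 355.49 = 116.51 m.
- SD: root mean square of the two SDs in the traditional-exercise study, √((52.5² + 68²)/2) = √3690.1 = 60.75 m. The PR study's SDs give √((62.56² + 56.72²)/2) = 59.71 m, so the choice matters little.
- Patients per arm: 40 analysed. This reads the lower stated figure as per group (40/(1 − 0.20) = 50, and 3 × 50 = 150). Fifty per arm is the case without dropout.
- Assumptions: equal arms, normal data, common SD.
- Smaller PR effects of 30, 40 and 50 m are assumptions, to show the range.

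**2. Omnibus test when Baduanjin does nothing.** Take means (0, 0, d) for control, Baduanjin and PR. The squared deviations from the grand mean sum to (2/3)d², so the noncentrality is λ = n × (2/3)d²/SD². Power is the probability that a noncentral F with 2 and 3n − 3 degrees of freedom exceeds the 5% critical value, which is 3.07 at n = 40.

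For d = 116.51 and n = 40: (2/3) × 116.51² = 9049.7, and λ = 40 × 9049.7/3690.1 = 98.1.
For d = 40 and n = 40: (2/3) × 40² = 1066.7, and λ = 40 × 1066.7/3690.1 = 11.6.

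| True PR effect, Baduanjin = control | ANOVA significant, 40 per arm | 50 per arm |
|---|---|---|
| 116.51 m (section 2.2) | >99.9% | >99.9% |
| 50 m | 97% | 99% |
| 40 m | 86% | 93% |
| 30 m | 61% | 72% |

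**3. Does the result depend on Baduanjin?** In 20,000 simulated trials with PR at +116.51 m, the ANOVA was significant in 100% when Baduanjin equalled control, and again in 100% when Baduanjin truly added 16 m (the 580 − 564 m of section 2.2). The omnibus result is the same either way. In the first setting the direct Baduanjin vs control t test was significant in about 5% of trials, its nominal rate.

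**4. The fallback.** If the rank sum test were run on all three pairs at .05, with no global test first and no adjustment, the chance of at least one false positive when all arms are equal is about 12% (simulation, 40 per arm). With a Kruskal-Wallis gate in front, the same simulation gives about 5%.

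**5. Do the other two tests fill the gap?**
- The covariance analysis is used only if baselines turn out unequal, and it refers to a pair of groups in a three-arm trial without saying which pair.
- The chi-squared test concerns a rate that the article does not define.

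Neither is a prespecified test of Baduanjin against control or PR on 6MWD.

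**The case against.** The strongest reply is that an omnibus first step is legitimate. With exactly three groups, pairwise tests carried out only after a significant ANOVA keep the familywise error at the nominal level without further adjustment. Pairwise comparison is plainly intended, since the Discussion says so, and follow-up contrasts may be set out in an analysis plan that is not shown. That stands, and it limits the point to a mismatch between the test stated and the hypotheses stated. It does not show that no contrast exists anywhere, and a gated procedure is one of the acceptable remedies below.

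It may also be said that Kruskal-Wallis was simply misnamed. That is quite possible, and the correction is then one term. The text as it stands still cannot be carried out on three groups.

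Four stronger readings are tempting but not supported:
- A reader might infer that ANOVA is the only between-arm test. Section 2.12 also names the covariance analysis and the chi-squared test, although neither closes the gap.
- A reader might infer a familywise error of 12% for the plan. That figure holds only for ungated, unadjusted pairwise tests, which the text does not specify.
- A reader might infer that a non-significant Baduanjin vs PR result will be presented as equivalence. No section plans an equivalence or non-inferiority claim.
- A reader might add that the Baduanjin contrast is too weakly powered. That is a question about the sample size in section 2.2. It does not depend on which test is named, and the change proposed here would not alter it.

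**Conclusion.** The concern holds as a mismatch between method and question. The test that section 2.12 assigns to the three-group comparison does not address the pairwise hypotheses in section 2.2 and the Discussion. On the protocol's own PR effect it is significant almost with certainty even if Baduanjin has no effect; with assumed PR effects of 30 to 50 m, it is significant in 61% to 97% of trials at 40 per arm. The omnibus P value therefore cannot be used as evidence for Baduanjin. Separately, the named fallback is the wrong procedure for three groups.

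The figures assume equal arms, normal data, a common SD near 60.75 m, and 40 to 50 patients per arm. The argument itself needs none of these: a global test does not identify which arm differs.

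**What to change.** In section 2.12, base inference on named pairwise contrasts of 6MWD at 12 weeks:
- Baduanjin vs control is the primary contrast, and PR vs control is also tested.
- Control multiplicity with Holm across these two contrasts (smaller P value against .025, then the other against .05). Alternatively, since there are three arms, test the pairs at .05 only if the ANOVA is significant. Either route keeps PR vs control from depending on Baduanjin succeeding, as it would in a fixed sequence with Baduanjin first.
- Report Baduanjin vs PR as an estimated difference with its 95% CI.
- Replace the rank sum fallback with Kruskal-Wallis followed by the same pairwise rank-sum contrasts under the same multiplicity rule.
- State that the omnibus P value alone will not be taken as evidence for Baduanjin.

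The change is to wording only and needs no further patients or data. It should be made before outcomes are compared by arm. The cost is a slightly stricter threshold per contrast under Holm, or, under the gated version, that no pair is tested unless the global test succeeds.
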